**Table 1. Testing Schedule**

|  | Screen | Baseline | Wk 1 | Wk 3 | End-Intervention  (Wk 6) | Follow-up  (Wk 10) |
| --- | --- | --- | --- | --- | --- | --- |
| Height | X |  |  |  | X | X |
| Weight | X |  |  |  | X | X |
| Demographic Questionnaires | X |  |  |  |  |  |
| PA/Sed Questionnaires | X | X | X | X | X | X |
| BSQ |  | X | X | X | X | X |
| RRV_video games_ |  | X |  |  | X | X |
| RRV_active games_ |  | X |  |  | X | X |
| Physical activity monitor |  | X | X | X | X | X |
| Debriefing |  |  |  |  |  | X |

**iv: Intervention:**

Participants will be randomly assigned to a high or low-autonomy group. Children in each group will be given an active video game system to use while enrolled in the study, and active video game DVDs requiring full body movements to operate. To evaluate whether AVG play impacts their motivation to engage in sedentary screen-based activities, children will also be given sedentary video games which can be operated using only hand and finger movement. To better simulate naturalistic conditions, the intervention will take place in participants’ homes. After both baseline RRV_activite games_ and RRV_video games_ have been assessed the intervention will commence. A researcher will visit the home at baseline to explain the intervention, set-up the AVG system, train the child and a parent on use of the system, and provide the activity monitor that the child will wear throughout the first, third, and sixth week of the intervention to track physical activity and sedentary behavior. The researcher will also provide a log and ask the child to record the date, duration of play, which game was played, and with whom as a check of study fidelity (Appendix 17). The researcher will stress to the child and parent the importance of following the research protocol, including wearing the activity monitor and recording AVG/video game play.

Children in the high autonomy group will be given two AVG games of their choice. Children in the low autonomy group will be given their most-liked game from the previous baseline RRV assessment. After two weeks, a researcher will return to the home to monitor progress and exchange the AVG and sedentary games. At each exchange, children in the high autonomy group will be allowed to select their next game, while children in the low autonomy group will receive a pre-determined game.

To facilitate the relatedness component of self-determination theory, children (both groups) will be encouraged to play the games with others, such as siblings, friends, or parents, and record with whom they played in the provided log. In the high autonomy condition, the children will be instructed to play the AVGs three times per week for a minimum of 20 minutes. Children in the low autonomy condition will be instructed that they must play three times per week for 20-40 minutes. Neither group will be given a specified time minimum or maximum minutes of play for sedentary video games. Additionally, children will not be told to play AVGs at any particular intensity, merely to record when and for how long they played the game, and to wear their activity monitors on the appropriate days.

Both groups will be given their highest liked sedentary video game from the baseline intervention. Parents will be discouraged from placing time limits on their children’s sedentary video game activities or taking away videogames as punishment for the duration of the study period, although parents need not make this known to the child.

*Post-Intervention Period:* During the four week post-intervention period, children will be provided with two AVGs and two sedentary games of their choice and told to play for however long and in whatever fashion they choose. Children will be asked to continue recording their play in the activity log. Parents will be told to not purchase or provide other AVGs or sedentary video games for their children during the intervention phase of the study, but they will be able to provide additional videogames during the four week post-intervention assessment. If additional video games are purchased, participants will be asked to report which games (active or sedentary) were bought and how much time was spent playing them. If there are already AVGs or sedentary video games in the household, participants will be asked to not play them until the end of the 6 week intervention, but can play them during the post-intervention period.

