**v: Measurements:**

**Height and Weight.** Body weight will be measured via a Tanita scale after voiding. Participants will wear t-shirts, shorts and no shoes during measurement. Height will be measured using a stadiometer. BMI percentile will be calculated based upon growth curves for each participant’s age and gender (Kuczmarski et al., 2000).

**Active Video Game (AVG) Reinforcement Task.** Participants will be given a list with 4 AVGs and 4 age-appropriate sedentary video games. Participants will sample and then rate their liking for each game on a scale of 1-10, with greater scores indicating a greater preference for that game. The highest liked active and sedentary videogames will be made available during the testing session. Participants will then play a slot-machine style game in which mouse clicks earn them time towards their most-liked game. Two computers will be set up, one for sedentary and one for active video games. Participants will be permitted to move freely between the computers.

During the game, three shapes of different colors will appear upon the screen. The participant will click upon the shapes in an attempt to make the shapes/colors match. Each match will earn one point, with 5 points earned at a particular schedule translating to minutes in each activity (in five minute intervals). Participants will be permitted to earn as much time with each game as they choose. The RRV of each game will be assessed by total responses and by maximum level completed (Pmax) which a participant is willing to make in order to earn minutes of play in their desired activity. Reinforcing value is measured using progressive ratio schedules of reinforcement. At first, points are delivered after every 4 presses, but then the schedule of reinforcement doubles (4, 8, 16, 32, […] 1024) each time 5 points are earned.

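### The high-autonomy arm starts with two active video games and the low-autonomy arm with one, so a week 6 difference cannot be attributed to autonomy alone

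*Protocol*

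**What the plan says.** The initial supply is set out in Protocol section C.iv (Intervention). For the high-autonomy arm: "Children in the high autonomy group will be given two AVG games of their choice". The low-autonomy entry is in the singular: "Children in the low autonomy group will be given their most-liked game from the previous baseline RRV assessment".

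The supply is then changed during the 6 weeks. At a home visit two weeks into the intervention, "a researcher will return to the home to monitor progress and exchange the AVG and sedentary games". The rule at each exchange is that "children in the high autonomy group will be allowed to select their next game, while children in the low autonomy group will receive a pre-determined" one. The staff-time list in section H shows check-ups at 2 and 4 weeks, so two exchanges are expected.

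The same section says of sedentary games: "Both groups will be given their highest liked sedentary video game from the baseline intervention".

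The arms also differ in their play-time instruction. In the high-autonomy arm "the children will be instructed to play the AVGs three times per week for a minimum of 20 minutes"; the low-autonomy arm is told that it must play at the same frequency for 20 to 40 minutes.

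During the 6 weeks parents are told not to provide other AVGs, and any already in the household are to be left unused. In the four weeks afterwards every child receives two AVGs and two sedentary games of his or her own choice, with no distinction between arms.

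**The concern.** H1a, the primary hypothesis, ascribes a rise in the reinforcing value of AVGs to high autonomy of play. Section A describes autonomy as choice over the manner and timing of an activity and does not mention how many games a child has. If one arm also has more games, any benefit of variety is credited to autonomy.

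The Protocol's own background makes variety a credible rival explanation: it reports that children often find AVGs boring and lose interest in them. A second title could slow that loss whoever chose it. The same problem applies to the other H1 comparisons between arms during the intervention.

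**Working it through.** No stated figure is in dispute, so the check is a comparison of what each arm receives.

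| Item | High autonomy | Low autonomy | Differs by arm? |
|---|---|---|---|
| AVGs at start | 2 | 1 | Yes, in number |
| Who selects the first AVG | Child | Assigned: baseline favourite | Yes, intended |
| AVG at exchange | Child selects; singular | Pre-determined; singular | Selection yes; number unclear |
| Sedentary game at start | Baseline favourite | Baseline favourite | No |
| Sedentary game at exchange | Not clearly stated | Not clearly stated | Unclear |
| AVG session length | At least 20 min | 20–40 min | Yes, part of the manipulation |
| Other AVGs, weeks 1–6 | Not to be used | Not to be used | No |
| Supply after week 6 | 2 AVGs and 2 sedentary, own choice | Same | No |

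**Number supplied.** At the start the counts are 2 and 1. If the singular wording at the two exchanges is taken literally, the totals over three two-week blocks are 2 + 1 + 1 = 4 and 1 + 1 + 1 = 3.

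**Can the analysis separate the two?** Section D has one between-subjects factor, high versus low autonomy. Every high-autonomy child starts with two games and every low-autonomy child with one, so initial number is an exact function of arm. No covariate, and no use of the play log, can estimate it separately.

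**Does follow-up repair it?** The week 6 RRV test closes the intervention, before the equal supply has had any effect. At week 10 the current supply is equal, but the earlier exposure still differs.

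**Illustration of size (assumed values).** Suppose autonomy has no effect and the extra game alone shifts the outcome by d standard deviations. The inputs are n = 25 per arm and alpha = 0.05 (section D). I assume a two-sided test, because sidedness is not stated, and a simple two-sample t test in place of the planned repeated measures ANCOVA.

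- Degrees of freedom: 2 × 25 − 2 = 48.
- Noncentrality: d × √(n/2) = d × √12.5 = 3.536 d.
- Probability of significance: the chance that a noncentral t falls outside the two-sided 5% critical values.

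| Assumed d | Noncentrality | P(significant arm difference) |
|---|---|---|
| 0.2 | 0.71 | 11% |
| 0.3 | 1.06 | 18% |
| 0.5 | 1.77 | 41% |
| 0.8 | 2.83 | 79% |

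The nominal rate is 5%. The documents do not say which d, if any, is realistic.

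**The case against.** The best defence is that a second game is part of delivering autonomy: a child with one title cannot choose what to play in a session. Autonomy is built here as a package of game selection and play-time instruction, and the arm comparison remains a valid randomised test of that package. This stands as far as it goes. It rules out the inference that the trial cannot answer its own question. It does not remove the problem, because the Protocol nowhere names number of games as part of autonomy.

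Three other stronger readings are tempting and are not supported.

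- *The two-to-one ratio lasts all six weeks.* It is explicit only at the start. At exchanges the wording is singular for both arms.
- *The arms differ in choice of sedentary games.* The exchange sentence follows one that covers both kinds of game, so a reader might infer this. But the first sedentary game follows the same rule in both arms, and the select-or-assigned sentence can equally be read as referring to AVGs. This is ambiguous wording, not an established difference.
- *The low-autonomy arm tires of the game used in the RRV test.* In that test "The highest liked active and sedentary videogames will be made available during the testing session", and the low-autonomy child starts at home with the baseline favourite. But ratings may be repeated at week 6, the favourite is due for exchange after two weeks, and high-autonomy children may choose their favourite too. The documents do not show that exposure to the tested game differs.

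**Conclusion.** The concern holds in this form: AVG quantity and variety are confounded with the autonomy label from the start of the intervention, and a week 6 difference in RRV cannot be attributed to autonomy alone. The explicit size is two games against one at the initial supply, or four against three in total if the exchange wording is literal.

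The conclusion assumes that the low-autonomy singular means one game and that families follow the rule on other AVGs. It does not depend on the illustrative probabilities, which rest on assumed effects. How large the distortion of H1a would be is unknown. Analysis cannot correct it after data collection, so it should be settled before the first child is supplied.

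**What to change.** 1. Supply the same number of AVGs to both arms at the start and at each exchange, and state that number; it is the sponsor's choice. Game supply then differs only in who selects. The play-time instructions remain as the other stated part of the autonomy manipulation, so selection would still not be the only difference between arms.
2. If unequal numbers are kept, describe the contrast as autonomy plus game variety wherever H1 is stated, and limit the conclusions to match.
3. In either case, reconcile the exchange wording with the sedentary-game sentence: state that the select-or-pre-determined rule applies to AVGs only, and that sedentary games follow one rule in both arms.

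The cost is Protocol wording plus, if the low-autonomy arm is brought up to two games at the start, one more loaned game for each of its 25 children. More would be needed if a higher number were also set at exchanges. No visits are added.

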**B. Overall Objective and Specific Hypotheses to be tested**

The goal is to investigate how autonomy might be used to increase children’s intrinsic motivation towards active video games, active play, and/or sedentary activity. Specific hypotheses include:

**H1a (Primary):** High autonomy of AVG play will result in increased reinforcing value of AVGs relative to sedentary video games. Lower autonomy of AVG play will not show an increased reinforcing value of AVG relative to sedentary video games.

**H1b**: High autonomy of AVG play will increase intrinsic motivation to play AVGs relative to low-autonomy control condition.

**H1c:** High autonomy of AVG play will increase intrinsic motivation to engage in physical activity relative to low-autonomy control condition.

**H1d:** High autonomy of AVG play will result in more hours of AVG play during the follow-up phase relative to the low-autonomy control condition.

**H1e:** High autonomy of AVG play will increase usual physical activity during the follow-up phase relative to the low-autonomy control condition.

**H1f:** High autonomy of AVG play will result in increased reinforcing value of AVGs relative to traditional active games.

**H2a:** Increased reinforcing value of AVGs will result in increased reinforcing value of sedentary video games.

**H2b:** Increased reinforcing value of AVGs will result in increased hours/week spent playing sedentary video games.

**H2c**: Increased reinforcing value of AVGs will result in increased time spent in other screen-based sedentary activities (television, computer games, tablets/cell phones).

**H2d:** Increased time spent in screen-based sedentary activities will result in increased sweetened beverage/snack consumption.

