**Motivation for Sedentary Behavior**. Questions from the BREQ-2 (Wilson et al., 2006) will be modified so that the question refers to motivation towards sedentary behavior (non-active video games, television, computers etc.) rather than physical activity. Similar to motivation for AVGs, this questionnaire will be validated via Cronbach’s alpha, RRV correlations, and minutes spent in sedentary activity (see Appendix 8).

**Physical activity-related parenting behaviors.** Parents will fill in The Activity Support Scale for Multiple Groups (ACTS-MG) developed by Davison (2011). The ASSMG includes 12 items, 3 each in: Logistic Support (parents making provisions enabling their child to be physically active), Explicit Modeling (parents using their own behavior to encourage their child to be active), Use of Community Resources (make use of community resources to get their child to be active) and Restricting Access to Sedentary Activities. Cronbach’s alpha ranges from 0.69 to 0.88. Items are measured on a 4 point scale (0 = strongly disagree; 4= strongly agree) with higher scores showing greater parental support for physical activity. The scale has good overall factorial validity and internal consistency (Davidson et al., 2011) (see Appendix 10).

**Parent self-efficacy for exercise.** The Barriers Self-efficacy Scale (BARSE) (McAuley, 1992). For the BARSE they rate how confident they are that they could motivate themselves to exercise regularly, for at least three months, despite common barriers. The scale consists of 13 items measured on as 10 point percentages (0 = not at all confident; 100 = highly confident). Items are summed with higher scores indicating greater self-efficacy. Scores predict exercise behavior (McAuley, 1991). The scale has good internal consistency and validity (McAuley et al., 2010) (see Appendix 11).

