Major analyses for Hypothesis 2 will take the form of multilevel regression equations. The main independent variable will be the changes in total reinforcement value (Pmax) of AVGs. Covariates will include age, gender, baseline enjoyment of sedentary video games, baseline time spent playing sedentary video games and other screen-based activities. The primary outcome variables will be maximum level earned (Pmax) towards sedentary video games and minutes of sedentary video games played per week. Once again, results will be considered statistically significant at α = .05. Covariates will be considered statistically significant as evidenced by significant β coefficients and significant increases in R^2^ values. Categorical covariates will be dummy-coded according to the procedure outlined in Cohen et al. (2003).

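### The Hypothesis 2b model leaves out the baseline parental-restriction score the protocol already collects, although parents are asked to relax limits on sedentary games after baseline

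*Protocol*

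**What the plan says.** **The instruction to parents.** Protocol C.iv (Intervention) states, for both arms, that "Parents will be discouraged from placing time limits on their children’s sedentary video game activities". The same sentence extends this "for the duration of the study period, although parents need not make this known to the child".

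**The hypothesis and its model.** Section B states H2b as "Increased reinforcing value of AVGs will result in increased hours/week spent playing sedentary video games". For Hypothesis 2, section D specifies multilevel regression: "The main independent variable will be the changes in total reinforcement value (Pmax) of AVGs". It fixes the adjustment set: "Covariates will include age, gender, baseline enjoyment of sedentary video games, baseline time spent playing sedentary video games and other screen-based activities". Weekly minutes of sedentary video games are one of two primary outcomes for Hypothesis 2.

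**The score already collected.** Section C.v (Mediators and Moderators) describes the ACTS-MG: "The ASSMG includes 12 items, 3 each in" four domains, one of which is "Restricting Access to Sedentary Activities". Parents complete it at the screening and consent visit (C.iii), and Table 2 shows a single assessment day.

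**Use of parental support elsewhere.** After its list of dependent variables, section D names parental support for physical activity as one of three moderating covariates. It treats it as one construct and mentions no separate restriction score.

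**The concern.** Relaxing a limit can change play only where a limit existed. Take two children who report the same baseline minutes, one from a strict home and one from a permissive home. Once limits are relaxed, the first has more room to increase. Adjusting for baseline minutes does not remove this difference, because the two children have the same baseline value.

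The H2b predictor, change in AVG Pmax, is measured after allocation and is not randomised, so randomisation does not protect its slope. An omitted determinant of the outcome costs precision in any case. If it is also related to the predictor, it biases the slope. Here the determinant has a baseline proxy that is already collected, and the protocol itself fixes the covariate list that leaves it out.

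**Working it through.** **Inputs from the protocol.** N = 50 (25 per condition) and α = 0.05, both from section D. Sidedness is not stated, so two-sided is assumed. Three of the 12 ACTS-MG items are restriction items. The plan gives no power figure or correlation for H2b, so there is no stated figure to reproduce. Every correlation below is an assumption.

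**Step 1: order of events.** Baseline recalls belong to the screening and baseline visits (C.iii). The home visit that explains the intervention follows the baseline RRV tests (C.iv). The protocol does not date the instruction to parents. Its place in the Intervention section makes usual house rules the natural reading for baseline and relaxed rules the natural reading afterwards.

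**Step 2: precision.** The share of residual variance removed is r², where r is the partial correlation of restriction with the outcome.
- r = 0.3: 0.3² = 0.09, and the standard error is multiplied by √0.91 = 0.954.
- r = 0.4: 0.4² = 0.16, and the standard error is multiplied by √0.84 = 0.917.

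Confidence intervals would be about 5 to 8% narrower, before the small loss from one degree of freedom.

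**Step 3: bias, simple approximation.** If restriction has the same correlation with the outcome and with change in AVG Pmax, the spurious correlation is their product. With Fisher's z, the shift is atanh(r) × √(50 − 3).
- 0.3 × 0.3 = 0.09: shift 0.0902 × 6.856 = 0.619. Rejection rate = P(Z > 1.341) + P(Z < −2.579) = 0.090 + 0.005 = 0.095.
- 0.4 × 0.4 = 0.16: shift 0.1614 × 6.856 = 1.106. Rejection rate = P(Z > 0.854) + P(Z < −3.066) = 0.197 + 0.001 = 0.198.

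**Step 4: simulation of the H2b regression.** This is a single-level simplification with N = 50, 3,000 runs per cell and a true slope of 0. Assumed values:
- correlation of restriction with baseline minutes: −0.3 or −0.6;
- effect of restriction on the rise in minutes: 0.3 or 0.5 SD;
- correlation between ACTS-MG subscales: 0.25.

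The type I error ranges over the four combinations are:

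| Correlation of restriction with change in AVG Pmax | Restriction omitted | ACTS-MG total added | Restriction subscale added |
|---|---|---|---|
| 0 | 4.4–5.6% | 4.4–5.8% | 4.1–5.4% |
| 0.2 | 5.9–9.6% | 4.2–6.3% | 4.4–5.5% |
| 0.4 | 7.7–24.1% | 6.0–11.0% | 4.7–5.1% |

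The Monte Carlo standard error at 5% is √(0.05 × 0.95/3000) = 0.4 percentage points. With restriction omitted, the slope bias is essentially 0, then 0.04 to 0.10, then 0.08 to 0.19 SD down the rows.

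With a true slope of 0.3, no confounding, a restriction effect of 0.5 SD and a baseline correlation of −0.3, power is 0.52 without the subscale and 0.63 with it. That cell is favourable. Its squared partial correlation is 0.25 × 0.91/(0.25 × 0.91 + 0.75) = 0.233, so r = 0.48, above the 0.3 to 0.4 of step 2.

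**Step 5: can the total score stand in?** With four subscales of equal variance and common correlation c, the total correlates (1 + 3c)/√(4 + 12c) with any one of them. This gives 0.50, 0.66 and 0.79 for c = 0, 0.25 and 0.5. The squares are 0.25, 0.44 and 0.62, so the total carries 25 to 62% of the restriction variance.

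**The case against.** The strongest reply is that this is an optional covariate in a secondary, observational model. Much of that stands. Parents are discouraged from setting limits, not forbidden. Baseline minutes are already in the model and absorb part of the effect. The entry rule of at least 14 hours of screen time per week probably narrows the range of restrictiveness. During the six weeks children are also asked not to play games already in the home, so minutes could fall whatever the house rules. The dependence on prior restriction is therefore a plausible mechanism, not an established fact. Nothing in the documents supports a correlation of 0.3 to 0.4 between restriction and change in AVG Pmax.

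It can also be said that section D's general mention of parental support already covers this. It reaches at most the composite, which dilutes the restriction items (steps 4 and 5).

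A reader might infer more than the documents support:
- **H2c is affected in the same way.** The instruction names sedentary video games only. H2c concerns television, computer games, tablets and phones, and no passage asks parents to relax limits on those.
- **The Hypothesis 1 moderator should lose its three restriction items.** The ACTS-MG is a baseline measure, and a baseline moderator need not stay active during treatment. The protocol does not say that the 12-item total is the moderator, and it plans reliability checks for both totals and subscales. Removing items would depart from the scale whose validity it cites.
- **The randomised comparison is biased.** Both arms receive the same instruction.
- **The subscale measures video game limits exactly.** Only its name is visible, and the item wording is in an appendix that is not shown.

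**Conclusion.** The point holds for H2b only, as a low-cost improvement. The fixed covariate list omits a relevant baseline score that the trial already collects. The expected benefit is precision: 9 to 16% of residual variance if the partial correlation is 0.3 to 0.4. Protection against bias is conditional on a link between restriction and change in AVG Pmax. Without that link the type I error stays near 5%, and the upper figure of about 24% needs both the strongest assumed effect and a correlation of 0.4. The conclusion rests on three assumptions: baseline minutes reflect usual house rules, the instruction changes behaviour in at least some homes, and the subscale is a reasonable proxy for limits on video games.

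**What to change.** In section D, state that the three ACTS-MG Restricting Access items will be scored separately, and add that baseline score to the covariates of the H2b model for weekly sedentary video game minutes. Check the item wording in Appendix 10 first, to confirm that the items bear on game time. Make the change before outcome data are examined. It costs one scoring sentence, one covariate and one degree of freedom. It needs no new data and leaves the instruction to parents, the H2c model and the Hypothesis 1 moderators as they are.
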